**Figure 2 F2:**
[figure not shown]
Telenursing intervention and data collection.

The qualitative data concerning satisfaction are collected through interviews at the end of period 1, at T12, and at the end of period, 2 at T24. Interviews will be conducted by an experienced research nurse in a non-judgmental and respectful manner, and at a predetermined location where privacy can be ensured. An interview guide with specific, prompting questions has been developed to guide the interviews. These questions are in relation to how parents felt supported through the service they received. Each interview will be tape recorded so as to accurately capture the participants’ comments and will transcribed verbatim using standardized transcription.

#### Study protocol compliance monitoring

The importance of compliance with the study will be emphasized when participants are recruited and periodically during the intervention period
[75]. Parental and child compliance with their monthly telephone contacts and their scheduled visits to the outpatient clinic will be carefully monitored throughout the course of the study. Intervention group participants will be considered to have complied with the study protocol if at least 80% of scheduled TN calls have occurred. If non-compliance is noted, information will be gathered on underlying problems; the TN nurse will meet with a member of the research team and measures will be undertaken to rectify the situation. The same procedure will be used with participants who repeatedly fail to attend their appointments.

Newly diagnosed children may require more frequent medical consultations to monitor therapeutic and side effects. All consultations between scheduled study visits, as well as changes in treatment, will be recorded.

### Primary outcome measure

The study’s primary outcome is participant satisfaction (parent or adolescent). Cox’s IMCHB defines the concept of satisfaction with nursing care from the patient’s perspective. The degree to which nurses adapt their care to meet the specific needs of the parent, guardian, or child relates directly to satisfaction
[68]. Satisfaction is assessed using a mixed methods approach where both quantitative and qualitative data are gathered and analyzed separately, and then the different results are converged.

Client Satisfaction Questionnaire-8 (CSQ-8) is an 8-item version of the 18-item CSQ developed by Attkisson and Zwick
[76]. It was designed to measure global client satisfaction in service delivery and program evaluation; it is brief to administer, has good psychometric properties (as demonstrated in several studies), and has been translated and validated in several languages, including French
[77]. CSQ-8’s items are rated on a 4-point Likert-type scale giving a total score ranging between 8 (no satisfaction) and 32 (total satisfaction). This study’s primary quantitative comparison will be the proportion of subjects in the intervention group (TN) and the control group (standard practice) with total CSQ-8 scores ≥ 30, as well as comparison within subjects as measured by CSQ-8 at T0, T6, T12, T18, and T24.

Qualitative data will be collected via individualized semi-structured interviews (SSI) at the end of each study period (T12 and T24) to avoid any bias. SSI have been commonly used in evaluating health programs and are particularly useful for exploring people’s in-depth knowledge, experiences and understanding. They can supplement or substantiate other sources of data
[78]. Here, the objective of SSI will be to determine satisfaction with regards to affective support, health information, and support in decision-making received.

### Secondary outcomes measures

Measurement of the *Clinical health status* will be performed every three months as per standard practice. This will consist of a core set of standardized clinical assessments of disease activity and disease-specific quality-of-life measures. *Disease activity* will be measured using a core set of four measures using the standard, self-administered, disease-specific Juvenile Arthritis Disease Activity Score (JADAS). This includes: 1) a physician’s overall assessment of disease activity; 2) a patient/parent overall assessment of well-being (both measured using a 10 cm visual analogue scale); 3) the number of joints with active disease, and; 4) the erythrocyte sedimentation rate
[79]. The equivalent available disease-specific core set of measures will be used for conditions other than JIA
[31].

*Quality of life* will be measured using the French version of the Juvenile Arthritis Multidimensional Assessment Report (JAMAR) for parents (JAMAR-P) and for children aged between 11 and 18 years old (JAMAR-C). Both original versions of the JAMAR have been validated
[80,81] and translated using standardized translation methods
[82]. The JAMAR includes 15 patient-related outcomes: 1) a 15-item functional status questionnaire; 2) pain intensity; 3) a 10-item disease-specific quality-of-life outcome, including the physical and psychological domains; 4) child’s overall wellbeing; 5) presence of pain in joints; 6) morning stiffness; 7) presence of extra-articular symptoms (fever and rash); 8) perception of disease activity; 9) disease status at the time of visit; 10) evolution of the disease since previous visit; 11) list of medications taken; 12) medication side effects; 13) difficulties with medication administration; 14) school problems; 15) satisfaction with the illness outcome
[83].

*Adherence to treatment* will be measured using the Parent Adherence Report Questionnaire (PARQ) and the Child Adherence Report Questionnaire (CARQ) that have both been validated in English and French
[84,85]. The PARQ has been adapted to the local context with permission of the developers and includes four questions related to medication and exercise. Questions address perceived difficulties in following the various forms of treatment as well as the benefits of treatment. Each question is rated on a 10 cm visual analogue scale. The CARQ was developed from the PARQ to allow children ≥ 9 years old to respond to the questions themselves
[85].

*Telenursing service utilization* will be recorded in terms of number, time, and duration of calls, who made them, the nature of the call, decisions taken, descriptions of the plan of action.

*Other outcomes*. Demographic data about participants in TN and other calls will be recorded, including age, gender, cultural background, marital status, occupation, education, language spoken at home, and types of treatment.

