**Methods/Design:**

This randomized crossover, experimental longitudinal study will compare the effects of standard care against a novel telenursing consultation on children’s and family outcomes. It will examine children below 16 years old, recently diagnosed with inflammatory rheumatic diseases, who attend the pediatric rheumatology outpatient clinic of a tertiary referral hospital in western Switzerland, and one of their parents. The telenursing consultation, at least once a month, by a qualified, experienced, specialist nurse in pediatric rheumatology will consist of providing affective support, health information, and aid to decision-making. Cox’s Interaction Model of Client Health Behavior serves as the theoretical framework for this study. The primary outcome measure is satisfaction and this will be assessed using mixed methods (quantitative and qualitative data). Secondary outcome measures include disease activity, quality of life, adherence to treatment, use of the telenursing service, and cost. We plan to enroll 56 children.

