### Study objectives and hypotheses

This study aims to evaluate the effect of a telenursing intervention on the satisfaction and health outcomes of children with inflammatory rheumatologic diseases and their families. The primary objective is to evaluate the effects of TN on the children/adolescent’s and parents’ satisfaction with the care given for inflammatory rheumatic diseases. The secondary objectives are to evaluate the effects of TN on the child’s clinical health status, quality of life, treatment adherence, and service utilization.

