[43,69,73]. Two specialist nurses, each with more than 5 years experience in adult and pediatric rheumatology, will attend a three-day course to enhance their skills in verbal communication, strategies for questioning parents and adolescents, assessing the quality of interactions, and aiding decision-making. The telephone intervention process will be standardized and recorded for each participant. It will involve a comprehensive, systemic assessment of the participant’s needs, including basic elements such as the participant’s characteristics, the date, time, and nature of the call, as well as a detailed description of the symptoms, problems, or reasons for the call. Following this assessment, prioritization and a plan will be developed collaboratively. Finally, the plan’s outcomes will be evaluated (was advice followed?).

Participants in the experimental TN group will attend a face-to-face medical and nursing consultation at baseline (T0) and then receive a monthly telephone call for 12 months. The face-to-face visit involves the TN nurse meeting with the parents and familiarizing herself with the child’s clinical, social, and family situation. The TN nurse will call the participant a total of 12 times, once during the last week of each month. Furthermore, the parent (and/or child if mature enough) will be given a telephone number (except for the control group) to call, as and when necessary, during normal Monday to Friday office hours. The TN nurse on duty will answer these calls and provide the same service.

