#### Control group

Children in the control group will receive the same standard care and services provided to all children and their families admitted to the rheumatology outpatient clinic. Children with rheumatic diseases attend several appointments here and are followed up at varying time intervals depending on the progress of their disease, but usually four times a year. Currently, the medical management of these children is provided mainly by a pediatric rheumatologist, but other specialists participate as determined by the child’s needs. Physiotherapists and occupational therapists are available and can refer patients to healthcare professionals outside the hospital.

At T0, control group participants will also have a face-to-face medical consultation at the pediatric rheumatology outpatient clinic, during which the study protocol will be clarified. The medical consultation will be repeated every three months as per current practice. Parents will be informed that they can call the outpatient clinic when necessary and speak a duty nurse. To avoid potential contamination between groups, control group parents will be assigned a telephone number other than the TN service number. Currently, duty nurses are clinical specialists in pediatrics with some rheumatology experience, but are not specifically trained in TN. The nature and frequency of all calls will be recorded in a logbook.

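### The service-utilization objective is comparative, but its outcome is defined as use of the telenursing line, which only the TN condition has

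*Protocol article*

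**What the plan says.** The section Study objectives and hypotheses lists the outcomes on which the effect of TN is to be evaluated. The list ends with "quality of life, treatment adherence, and service utilization".

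Two places give the outcome that corresponds to the last item. The abstract lists "adherence to treatment, use of the telenursing service, and cost" among the secondary outcomes. Secondary outcomes measures has an entry on telenursing service utilization, which "will be recorded in terms of number, time, and duration of calls, who made them, the nature of the call, decisions taken". No other entry in that section concerns use of services.

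The section Intervention describes the line. Families in the TN condition "will be given a telephone number (except for the control group) to call, as and when necessary". It also fixes the outgoing contacts: "The TN nurse will call the participant a total of 12 times, once during the last week of each month".

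Other sections describe records that are not tied to the TN line:

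- Control group: "Parents will be informed that they can call the outpatient clinic when necessary", on a different number, and "The nature and frequency of all calls will be recorded in a logbook".
- Data collection: telephone nurses record the frequency, duration and nature of calls made and received, and call records run through both periods.
- Study protocol compliance monitoring: "All consultations between scheduled study visits, as well as changes in treatment, will be recorded".

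**The concern.** An effect of TN on utilization is a contrast between the TN and the control condition, so it needs a quantity that can take any value in either. Use of the TN line is not such a quantity. Under control the family is not given the number, so use is meant to be zero; under TN it starts from the scheduled calls. A difference between conditions in that outcome would describe how the trial was set up, not how families behaved.

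At stake is whether the trial can report that TN raises, lowers or replaces other use of care. An analyst who follows the outcome section literally would describe TN calls and leave the objective unanswered. One who follows the objective literally would have to choose the comparative measure later, possibly after seeing the data.

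**Working it through.** The article gives no expected rate of calls or consultations, so there is no utilization figure to reproduce. The check sets the sections side by side and then does simple count arithmetic.

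**Step 1. Which measures exist in which condition?**

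| Measure | TN condition | Control condition | Source |
|---|---|---|---|
| Scheduled TN calls | 12 per year | none | Intervention |
| Family calls to the TN line | possible, recorded | number not given | Intervention; Secondary outcomes measures |
| Family calls to the clinic line | logging not stated specifically | possible; nature and frequency logged | Control group |
| Call records in general | both periods | both periods | Data collection |
| Consultations between scheduled visits | recorded | recorded | Study protocol compliance monitoring |

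The named outcome covers the first two rows only. The rows that allow a comparison are not named as the outcome in any section.

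**Step 2. What would a raw call total show?**

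Let u be the number of family-initiated calls per family per year. The article does not give u, so I assume a range and suppose that TN has no effect on it.

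- Total under TN: 12 + u
- Total under control: u
- Difference: (12 + u) − u = 12, whatever u is
- Ratio: (12 + u) / u

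| u (assumed) | TN total | Control total | Difference | Ratio |
|---|---|---|---|---|
| 1 | 13 | 1 | 12 | 13 |
| 2 | 14 | 2 | 12 | 7 |
| 4 | 16 | 4 | 12 | 4 |
| 6 | 18 | 6 | 12 | 3 |

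For a family just meeting the 80% compliance threshold, 0.8 × 12 = 9.6, so about 10 scheduled calls remain in the total.

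**Step 3. Can the artefact be removed with the data as specified?**

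Yes. The outcome entry records who made each call, and Data collection distinguishes calls made from calls received. With scheduled calls set aside, the comparison is u under TN against u under control, a difference of 0 when there is no effect.

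**Step 4. Which features are comparable?**

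For TN calls the entry lists number, time, duration, caller, nature and decisions. For the clinic logbook, Control group promises only nature and frequency. Counts are therefore the safe common measure; duration and decisions may not be available on both sides.

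**The case against.** The best reply is that the outcome entry is a descriptive process measure. Reporting how often, by whom and for what a new service was used, in the condition that offers it, is legitimate. On that reading the only weakness is a loose phrase in the objectives. It can be added that a condensed article may leave the construction of a secondary count, and the choice of count model, to a fuller document that is not shown.

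Part of this stands. Descriptive reporting of TN use is sound and should be kept, and a missing count model would be no finding on its own. But the article does not leave the outcome open: it states one, in the abstract and again in the outcome section, and that outcome exists in one condition while the objective asks for an effect. Either the objective or the outcome has to change.

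Two stronger readings are tempting, and the article supports neither. A reader might infer that utilization is captured only through the TN line, so that no effect of TN on it can be estimated. The clinic logbook, the call records in both periods and the record of unscheduled consultations contradict that. A reader might also infer that a bias of 12 calls is built into the results. No section says that totals including scheduled calls will be compared, and those calls can be separated.

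**Conclusion.** The point holds as a mismatch between a comparative objective and an outcome defined in one condition. The defect lies in the definition, not in data capture.

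Its numerical size is conditional: 12 calls per family per year (about 10 at the compliance threshold) if total calls were compared, and none if only family-initiated calls are. The ratios of 13 down to 3 rest on assumed values of 1 to 6 family calls a year and on no true effect.

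The comparison also rests on clinic-line calls being logged while a family is in its TN period. The general statement on call records suggests this, but the logbook is described only under the control condition.

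This is a secondary outcome. The primary satisfaction analysis and the sample size do not depend on it.

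**What to change.** 1. Define the comparative utilization outcome as (a) family-initiated calls to either the TN line or the clinic line and, separately, (b) consultations between scheduled visits. Count both by the same rules in both conditions.
2. State that clinic-line calls are logged during the TN period as well as the control period.
3. Analyse each count per 12-month period with a within-subject count model, for example mixed-effects Poisson or negative binomial, with treatment and period terms and a random effect for the family. Every family receives both conditions, so a plain between-group comparison would waste the pairing and ignore the period effect.
4. Report TN-line use and the 12 scheduled calls descriptively, as delivery of the intervention.
5. Word the abstract, the objective and the outcome section alike.

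The cost is a revised definition, one model form applied to two counts, and an instruction to keep the clinic logbook in both periods. No new instrument, visit or participant is needed.

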### Sample size and power

In 2008, 113 newly diagnosed children were admitted to the study hospital’s pediatric rheumatology outpatient clinic. Of these, 48 were diagnosed with an inflammatory rheumatic diseases. Based on these numbers, it is anticipated that around 70 children will be admitted to the clinic in the 18-month screening period prior to enrolment into the study. If we consider that 80% of patients/parents will give consent to their participation, this would leave a pool of 56 families available for the two-year study period.

A power analysis was calculated based on the number of participants expected to complete the study, not the number recruited initially. If we consider a difference in the proportion of subjects in the two groups with a satisfaction score ≥30, e.g. 70% in TN versus 20% in the control group, then 23 subjects per group (total of 46 subjects) would be required to reach a power level of .90 for an alpha level of .05 (two-sided test). Effective strategies will be used to maintain the sample size. To compensate for an expected attrition rate of 20%, two groups of 28 subjects will be recruited (total of 56 subjects).

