## Methods/Design

### Study design

This study has a randomized crossover, experimental longitudinal design, in which the intervention (telenursing) is evaluated with the same subjects and so eliminates between-subject variability, in particular due to the heterogeneity of the disease
[6,65]. Crossover trials are particularly useful when the outcomes of interest are symptoms and functional capacity
[66].

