### Randomization and allocation of treatment

In crossover trials, both experimental and control experiments are given to every participant, randomizing the order in which they are applied
[65]. Consenting participants will be allocated treatment using a computer-generated simple block randomization. The benefits of using blocks are to ensure that the accrual of participants to either arm is uniform over time. An independent researcher, not involved in the recruitment or evaluation of follow-up, will prepare sealed, numbered envelopes containing an allocated treatment. Once randomization has occurred, blinding of participants and the caregiver is not feasible for this type of intervention, providing a potential risk for bias.

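### The 46 completers for power .90 come from a two-independent-groups formula; in this crossover neither figure describes the within-subject comparison, and the mismatch is conservative

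*Protocol article*

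**What the plan says.** Under Sample size and power, the article assumes "e.g. 70% in TN versus 20% in the control group" reaching the satisfaction threshold, "for an alpha level of .05 (two-sided test"), and concludes "then 23 subjects per group (total of 46 subjects) would be required to reach a power level of .90". The 46 are completers, not recruits: "A power analysis was calculated based on the number of participants expected to complete the study, not the number recruited initially". Recruitment is then set at 28 per group, 56 in total, for 20% attrition. The section gives no within-subject correlation or share of discordant pairs.

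The design sections describe a different structure. Under Study design, "the intervention (telenursing) is evaluated with the same subjects and so eliminates between-subject variability". Under Randomization and allocation of treatment, "both experimental and control experiments are given to every participant", with the order randomized. Under Data collection, participants switch to the other condition after period 1. Under Primary outcome measure, the primary quantitative comparison is the proportion at or above 30 in TN and in control, together with a within-subject comparison of CSQ-8 over T0 to T24. Under Hypotheses testing, mixed effect linear models are planned to deal with carry-over and time effects. No section limits the powered comparison to period 1.

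**The concern.** The sample size paragraph treats TN and control as two separate sets of 23 people. In the crossover, the randomized groups are order groups, and after both periods 46 completers provide 46 TN and 46 control responses, in pairs. The precision of a paired comparison depends on how the two responses of the same subject go together, which the calculation leaves out.

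At stake is what the .90 refers to. If it is the within-subject comparison, the stated power and required size are both wrong for it, and the reader is not told that the trial could detect a smaller difference than the assumed 50 points. If it is a comparison of the two order groups in period 1, the figure is right but is not labelled as such, and the stated advantage of eliminating between-subject variability does not apply to it.

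**Working it through.** **Inputs from the article.** p1 = 0.70 (TN), p2 = 0.20 (control), two-sided alpha 0.05, power 0.90, 46 completers, 56 recruited, 20% attrition. Expected completers: 56 × 0.80 = 44.8, so 44 and 46 pairs are both shown.

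**Input not in the article.** The within-subject association. The margins 0.70 and 0.20 limit it: the share p11 of subjects above the threshold under both conditions can lie only between 0 and 0.20. That whole range is used as an assumption.

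**Step 1: reproduce the stated figure.** For two independent proportions with pooled mean 0.45:

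n = [1.96 × √(2 × 0.45 × 0.55) + 1.2816 × √(0.70 × 0.30 + 0.20 × 0.80)]² / 0.50² = 18.64

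With continuity correction: (18.64/4) × [1 + √(1 + 4/(18.64 × 0.50))]² = 22.46, so 23 per group. This matches the article exactly. The uncorrected formula would give 19.

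**Step 2: the paired comparison at the same rates.** Let p10 = 0.70 − p11 be the share above the threshold under TN only, p01 = 0.20 − p11 the share above it under control only, and ψ = p10 + p01. The normal approximation for McNemar's test is

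n = [1.96 × √ψ + 1.2816 × √(ψ − 0.50²)]² / 0.50²

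- Strongest positive association: p11 = 0.20, ψ = 0.50, n = 16.4, so 17.
- Independence: p11 = 0.70 × 0.20 = 0.14, p10 = 0.56, p01 = 0.06, ψ = 0.62, n = 21.6, so 22.
- Strongest negative association: p11 = 0, ψ = 0.90, n = 33.5, so 34.

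The approximation is slightly optimistic. By the exact McNemar test, 22 pairs at independence give only 0.874. The exact results are:

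| Association | ψ | Total completers for .90 | Power, 44 pairs | Power, 46 pairs |
|---|---|---|---|---|
| Strongest positive | 0.50 | 17 | about 1.00 | about 1.00 |
| Independence | 0.62 | 24 | 0.997 | 0.998 |
| Strongest negative | 0.90 | 38 | 0.945 | 0.956 |

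Under every association that the two rates allow, the required total is below 46 and the power at 44 or 46 pairs is above .90.

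**Step 3: detectable difference.** With control at 20% and independence, 44 pairs give 0.912 for 56% and 46 pairs give 0.910 for 55%. So about 55–56% versus 20% is detectable with .90, a difference of 35–36 points rather than 50. This depends on the assumed association. For 44 pairs and 56% versus 20%, power is 0.82 at correlation −0.3, 0.91 at 0 and 0.97 at 0.2.

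McNemar's test is used here as a simple paired benchmark. It ignores period and carry-over effects and is not the mixed model that the article plans.

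**The case against.** The best defence is that nothing was miscalculated. The inputs, alpha, sidedness and result agree, and the TN-versus-control proportion is named first under Primary outcome measure, with the within-subject comparison added to it. If the first is read as a comparison between groups, the paragraph fits it. Sizing a crossover by the more demanding parallel formula can also be a cautious choice when the correlation is unknown. The 56 also equals the expected pool of consenting families (70 × 80%), so another formula might not have changed recruitment.

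Much of this stands: the arithmetic is correct and the choice errs on the safe side. It does not remove the point. The article never restricts the comparison to period 1, it counts completers of the whole study, and it does not present the parallel formula as a deliberate conservative choice.

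It is also fair to say that a McNemar figure does not describe the planned mixed model. That is a reason to label any paired figure as approximate, not to leave the parallel one standing as the power of the crossover.

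**Conclusion.** The stated power and required size do not describe the within-subject comparison that is part of the primary analysis. At 70% versus 20%, .90 needs about 17 to 38 completers in total for that comparison, not 46, and 44 to 46 pairs give power of 0.945 to about 1.00. These figures assume an exact McNemar test, no carry-over or period effect, and any within-subject association that the two rates allow.

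Three stronger readings are tempting and are not supported.

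- A reader might infer that the trial is underpowered. The error goes the other way under every possible association.
- A reader might infer that the paired power is simply above .99, or that 22 subjects would do. The first holds at independence or positive association but not over the whole range; the second fails the exact test even at independence.
- A reader might infer that the period-1 comparison is, or should become, the primary one because it fits the .90. The article nowhere says so, and it would go against the within-subject rationale given under Study design.

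This is a definite misstatement that is cheap to correct, with no consequence for the number recruited.

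**What to change.** Keep 56 recruits and the crossover analysis, and restate the paragraph under Sample size and power:

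1. Say that 23 per group for .90 is a parallel-group calculation, of the kind that would apply to period 1 alone, and that it is conservative for the within-subject comparison.
2. Give the paired power at the expected 44 to 46 completers as a range over the assumed within-subject association (0.945 to about 1.00 for 70% versus 20%), and say that it ignores period and carry-over effects.
3. If a detectable difference is quoted, such as about 55–56% versus 20%, name the association behind it and show how the power changes when the association does.

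Do not make the period-1 comparison primary merely to fit the figure. The cost is one rewritten paragraph, with no change to recruitment or to the planned analysis.

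### Recruiting 56 covers about 18% attrition, not the stated 20%: a small correction to the sample size statement, with little effect on power

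*Protocol article*

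**What the plan says.** All the relevant figures are in the protocol article, section Sample size and power.

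- Basis of the calculation: "A power analysis was calculated based on the number of participants expected to complete the study, not the number recruited initially".
- Effect assumed for a satisfaction score of at least 30: "70% in TN versus 20% in the control group".
- Requirement: "then 23 subjects per group (total of 46 subjects) would be required", for power of .90 and "for an alpha level of .05 (two-sided test").
- Recruitment: "To compensate for an expected attrition rate of 20%, two groups of 28 subjects will be recruited (total of 56 subjects").

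The same section separately arrives at 56 available families, by applying an 80% consent rate to about 70 eligible children.

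**The concern.** Because the section says that the requirement counts completers, the recruitment target has to leave 46 people after the expected losses. The number to recruit is then the requirement divided by the proportion retained. The stated target falls below that, so 46 completers, 20% attrition and 56 recruits cannot all hold together.

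What is at stake is the accuracy of the stated allowance. A reader is told that 20% attrition has been covered, and on the section's own numbers it has not quite been. If the gap were large, the trial would also fall short of its stated power, so the size of the gap has to be checked.

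**Working it through.** **Inputs**, all from Sample size and power: 70% versus 20%; two-sided alpha 0.05; power 0.90; 23 completers per group (46 in total); 20% attrition; 28 recruited per group (56 in total).

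**Step 1. Reproduce the 23 per group.** With p1 = 0.70, p2 = 0.20 and mean 0.45, the usual two-proportion formula is

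n' = [1.96 × √(2 × 0.45 × 0.55) + 1.2816 × √(0.21 + 0.16)]² / 0.50² = 18.64, rounded up to 19.

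With the continuity correction,

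n = (n'/4) × [1 + √(1 + 4/(n' × 0.50))]² = 22.46, rounded up to 23.

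The stated 23 is therefore reproduced exactly by the continuity-corrected formula. The unrounded requirement is 22.46 per group, or about 44.9 in total.

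**Step 2. Check the attrition allowance.**

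- Completers from 56 at 20% loss: 56 × 0.8 = 44.8 (22.4 per group), which is 1.2 below 46.
- Attrition that 56 can absorb: 1 − 46/56 = 17.9%.
- Recruits needed for 20% loss: 46/0.8 = 57.5, so 58. Per group, 23/0.8 = 28.75, so 29.
- Alternative that gives the stated figure: 23 × 1.2 = 27.6, so 28 per group and 56 in total.

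The target equals the result of multiplying by 1.2. It does not equal the result of dividing by 0.8.

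**Step 3. Effect on power**, for 70% versus 20% at two-sided 0.05:

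| Completers | Continuity-corrected formula | Exact (Fisher) |
|---|---|---|
| 23 + 23 = 46 (required) | 0.909 | 0.913 |
| 45, split 22/23 | 0.901 (at 22.5 per group) | 0.925 to 0.929, depending on which group has 23 |
| 22.4 per group (expected, 44.8) | 0.899 | not defined |
| 22 + 22 = 44 | 0.892 | 0.890 |

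The exact power is higher at 45 than at 46 because the test is discrete. It is not a real gain from having fewer patients. Without the continuity correction, power at 22 per group is 0.944, but that formula gives 19 per group and so is not the one behind the stated 23.

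**The case against.** The strongest reply is that this is a rounding matter. The unrounded requirement is 22.46 per group and the expected number of completers is 22.4 per group, so the design sits almost exactly at 0.90. Power falls below 0.90 by about one point only if completers are taken as 44 in two equal groups. With 45, exact power is above 0.90. The inputs are also approximate: the 70% and 20% are offered as an example, and 20% attrition is a round planning figure. Finally, the calculation treats the trial as two parallel groups, while each participant receives both conditions. A within-subject analysis may need fewer patients, although the gain cannot be computed because the article gives no within-subject correlation.

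This reply stands as far as power is concerned. A reader might infer from the shortfall that the trial is underpowered, and the figures do not support that.

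A reader might also take it as established that the planners multiplied by 1.2. The article does not say how 28 was reached. The same section obtains 56 families as 80% of about 70, so the target may equally reflect the expected pool.

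Neither point rescues the sentence itself. The section declares 46 to be a completer count and says that 56 compensates for 20% loss. No other section of the article changes either figure, and rounding up from the correct division gives 29 per group, not 28.

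**Conclusion.** The stated attrition allowance is wrong as written, by a small amount. With 56 recruits the plan covers about 18% attrition. At 20% attrition it expects 44.8 completers rather than 46, and full cover would take 58 recruits, two more than planned.

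The consequence for power is minor: 0.89 at worst (22 per group), essentially 0.90 at the expected number, and about 0.92 to 0.93 by exact test with 45 completers, against 0.91 at 23 per group.

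The mismatch rests only on the section's own figures. The power values rest in addition on its 70% versus 20% assumption and on a two-group comparison of proportions. The explanation by a factor of 1.2 is an inference from the matching number, and the finding does not depend on it. Severity is minor.

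**What to change.** Keep 56 as the recruitment target and make the sentence agree with it, in one of two ways:

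- State that recruiting 56 allows for about 18% attrition while keeping 46 completers.
- Keep 20%, and state that about 44 to 45 participants are then expected to complete, with power of roughly 0.89 or more under the same assumptions.

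It would help to add how the recruitment figure was obtained. The cost is one sentence. No extra patients are needed and nothing in the conduct of the trial changes.
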